### **2. Adverse events (AE)**

Adverse events (AEs): refer to all adverse medical events that occur in subjects during the course of a clinical study, which can be manifested by symptoms and signs, diseases or abnormal laboratory tests, and do not necessarily have a causal relationship with treatment.

Note: Planned surgery or hospitalization that existed prior to the subject's receipt of informed consent to participate in the clinical study but did not deteriorate during the study or was performed prior to the implementation of study entry into the study is not an adverse event.

### **3. Judgment of relevance of adverse events**

The relationship between AEs and the study drug was judged according to five levels of "definitely related, probably related, possibly related, probably unrelated, and definitely unrelated", and the incidence of adverse reactions was included in the first three levels.

**Affirmatively related:** AEs are consistent with the types of adverse effects common to the study drug, and their occurrence has a reasonable temporal relationship with the study drug, AEs disappear after discontinuation and are not related to concomitant medications or non-pharmacological factors (primary disease, complications, food, environment, etc.).

**Likely related:** AEs consistent with common types of adverse effects of study medication, reasonable temporal relationship with study medication, significant remission of AEs after discontinuation, and AEs unrelated to concomitant medications or non-pharmacological factors.

**Possibly related:** AE conforms to the common adverse reaction types of study medication and has a reasonable time relationship with study medication. The AE is not significantly relieved after drug withdrawal. The relationship between concomitant medication or non-drug factors and AE cannot be ruled out.

**Possibly unrelated:** The adverse reaction has a reasonable time relationship with the study drug, but does not meet the common adverse reaction types of the study drug. The AE is not relieved after stopping the drug. The AE can be explained by concomitant medication or non-drug factors.

**Irrelevant:** The AE has no reasonable time relationship with the study medication and does not meet the common adverse reaction types of the study medication. The AE is not relieved after discontinuation of the medication. The AE is definitely related to concomitant medication or non-drug factors.

### **4. Anticipated adverse events and treatment plans**

Anticipated Adverse Events: Adverse events that subjects may face while participating in the study. Possible

adverse events in this study and The handling measures are as follows.

(1) Local adverse events on teeth: mild inflammatory reactions such as mild redness and swelling of the gums; severe inflammatory reactions such as loose periodontal pockets and pus overflow, periodontal ligament edema, etc. The researchers conducted symptomatic treatment in accordance with the routine clinical diagnosis and treatment of periodontal disease: for mild inflammatory reactions in periodontal tissue, local irrigation of the periodontal pockets and gargling with mouthwash were performed; for severe inflammatory reactions in periodontal tissues, debridement of the periodontal pockets was performed. Antibiotics are built into the bag. If necessary, local abscesses can be incised and drained and gargled with mouthwash.

(2) Injection local hematoma: It manifests as injection local blood vessel damage, intra-tissue bleeding, and purple-red petechial or masses under the mucosa or subcutaneously. Principles of prevention and treatment: If hematoma has appeared locally, immediate compression can be used to stop the bleeding and cold compress should be applied; subjects are instructed to apply hot compress after 48 hours to promote the absorption and dissipation of the hematoma. Antibiotics and hemostatic drugs may be given as appropriate.

(3) Systemic adverse events: chills, fever, mild headache, which can subside naturally.

(4) Progression of periodontitis: During the study period, if the subject's periodontitis progresses, the researcher will judge whether to intervene or not. For example, other treatments or drugs may be used to intervene that may affect the study, or the researcher may evaluate whether to withdraw.

(5) In clinical drug research, a very small number of subjects may suffer from shock due to allergic reactions. Once a subject develops anaphylactic shock, treatment will be carried out in accordance with the "Anaphylactic Shock First Aid Plan Standard Operations".

## **5. Unexpected adverse events**

Unexpected adverse events: events that occur during clinical research and meet the following three criteria: ① The nature, severity and incidence are unexpected; ② Related or potentially related to participation in the study; ③ Subjects or others face greater risks. Big risk. In clinical studies, when the same adverse event occurs in multiple subjects, and the nature, severity, and frequency are not mentioned in the current investigator's manual or protocol as related to the study drug, the investigator should report it to the preparation preparation as soon as possible. The institution reports this adverse event. If the adverse event is confirmed to be an unexpected adverse drug reaction, the researcher should assist the preparation preparation institution to write a safety report and submit it to the drug regulatory department and ethics committee, and notify all researchers, and amend the protocol and informed consent form if necessary, while revising the Investigator's Manual to include new adverse reactions or changes in the frequency and severity of known adverse reactions.

## **6. Serious adverse events (SAE)**

Events that require hospitalization, prolong hospitalization, become disabled, affect work ability, endanger life or death, or cause congenital malformations occurrence during clinical research.

Note: "Life-threatening" in the definition means that the subject is in danger of death if the event occurs; it does not mean that if the event is serious, it will lead to death.

## **7. Important adverse events**

In addition to serious adverse events, any adverse events that result in targeted medical measures (such as discontinuation, dose reduction, and symptomatic treatment) and significant abnormalities in hematology or other laboratory tests.

Note: Medical and scientific judgment should be used to determine whether an event is a medically important event.

An important medical event may not necessarily be immediately life-threatening and/or result in death or

hospitalization. However, if it is determined that an event may harm the subject or may require medical intervention to prevent the occurrence of any of the above serious adverse event outcomes, then the important medical event should be reported as a serious adverse event.

## **8. Requirements for recording adverse events**

From the time the subject signs the Informed Consent Form (ICF) until the end of the study, regardless of whether or not the subject receives treatment with stem cell preparations, both Adverse Events (AEs) should be recorded regardless of whether they are observed by the investigator or reported by the subject. The investigator should fill in truthfully during the study. The type, degree, time of appearance, duration, treatment measures and treatment history of AEs should be recorded in detail. The comorbidities should be considered in a comprehensive manner, combined medications and evaluate their relevance to DPSCs preparations.

All physical examination and laboratory test results required by the clinical research protocol should be recorded in the original medical record of the subject. Compare the subject's physical examination results and laboratory tests after the local injection treatment with the results before the local injection treatment. If the change is suggestive of a deterioration in the subject's clinical status, the Investigator must evaluate to determine if it meets the definition of AEs. All changes determined to meet the definition of an AEs will be documented in the AEs section of the original medical record.

Medical documentation of AEs should be documented in the original file, including oral periodontal exams, blood exams, imaging, and CBCT exams. Examination notification forms and results report forms for CBCT examinations. If the subject is unable to continue to treatment by the Investigator, etc., the Investigator shall submit a summary of the subject's medical record (including treatment schedule and indication of the need for continued follow-up of adverse events, etc.) to the person in charge of the study (including a description of the treatment schedule and the need for continued follow-up of adverse events, etc.) to the physician responsible for their continued treatment. This information should also be recorded in the original documentation.

AEs need to be followed up by the investigator to the baseline level or to the final outcome.

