|                           | 
1. Saline iniectio group: immediately after the completion of basic periodontal treatment Injection, therapeutic dose of 0.6mL saline / dental position / person, 10 subjects;
 
2. Single DPSCs injection group: Bilateral multi-point injection was performed on a single tooth position of the subject immediately after the completion of basic periodontal treatment ejaculation, with a therapeutic dose of <math>1 \times 10^7</math> hDP-MSC cells (saline 0.6mL suspension)/dental position/person, 10 subjects were enrolled;
 
3. Double DPSCs iniectio group: Immediately after the completion of periodontal basic treatment, bilateral multi-point injection was performed on the single tooth of the subject, and the therapeutic dose was <math>1 \times 10^7</math>hDP-MSC cells (0.6mL saline suspension)/tooth position/person. A month later, bilateral multi-point injection was performed on the single tooth of the subject again. The therapeutic dose was also <math>1 \times 10^7</math> HDP-MSC cells (0.6mL suspension of normal saline)/dental position/person, and 30 subjects were enrolled.
 
In summary, in the two stages of this study, about 33 subjects are expected to be included in the normal saline control group, about 33 subjects in the stem cell treatment group, and 30 subjects in the stem cell secondary administration group, meeting the requirements of statistical analysis.
 
(2) Design of cell therapy dose
 
According to the results of previous studies, the local cell injection cell dose is: 1107Cell / 0.6 mL / tooth position / human.
 
(3) Blind setting: This study was an open study, and only periodontal data collection personnel and image data measurement personnel were kept blind. In this study, the appearance of human dental pulp mesenchymal stem cell preparations after suspension before use was pale milky uniform suspension, and the appearance of normal saline control was colorless clear liquid, so it was impossible to implement blind method for subjects and researchers conducting local injection operations.
 |

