## (7) Attrition.

**4. Translation Assignment Grouping Method:** In this study, a block randomization method was used at each stage, and the randomization was generated by a statistician using SAS 9.4 software. The randomization and grouping coding were implemented in this study. In the first stage, subjects were assigned to either the stem cell treatment group or the saline control group in a 1:1 ratio based on the assigned coding. After completion of this stage, the randomization envelopes were collected by the statistical unit. In the second stage, subjects were assigned to the saline control group, stem cell treatment group, or stem cell re-administration group in a 1:1:1 ratio based on the assigned coding. The statisticians were not involved in the screening, inclusion of subjects, or subsequent clinical research. Throughout the study, the researchers responsible for the safety and efficacy data analysis maintained blinding.

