  - Immunology: IgA, IgG, IgM, Total IgE; During the screening period, before administration, 2h±30min after the end of administration, D30±5, D90±5, D180±5, D360±5, and the second dose group of stem cells in the second stage of this study 2h ±30min after the end of the second dose treatment.
  - Pregnancy test: blood β-HCG, premenopausal female subjects in the screening period, pre-drug, follow-up period D30±5, D90±5, D180±5 inspection.
  - Urine routine: PH value, specific gravity, protein, ketone body, bilirubin, urobilinogen, nitrite, white blood cells, red blood cells, urine glucose, urine sediment microscopic examination, during the screening period, before treatment.
- (3) For subjects with adverse reactions, timely treatment, follow-up inspection and recording should be carried out in accordance with the diagnosis and treatment routine.
- (4) Adverse events and serious adverse events: The occurrence of adverse events and serious adverse events was recorded in a timely manner during the study, and the degree of adverse events was determined according to the NCI CTCAE v4.03 grading standard. Swollen and painful gums within one week after surgery, recorded as an adverse event, judged by the investigator to be an administration-related adverse reaction.

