#### **(1) Analyzed Population:**

Statistical analysis datasets for the study results included the full analysis dataset (FAS), the protocol compliance dataset (PPS), and the safety Sexuality dataset (SS).

**Full Analysis Set (FAS):** for all cases that had used the study drug after enrollment and had completed at least one efficacy assessment. cases with at least one efficacy assessment completed after enrollment. The estimation of missing values for the main indicators was performed by the method of LOCF (last observation carrying forward).

**Per Protocol Set (PPS):** a subset of the FAS, all cases that comply with the study protocol,

have good compliance, do not use prohibited drugs during the study period, have completed 6 months of clinical observation, and have completed the CRF;

**Safety Set (SS):** all cases that received the study drug after enrollment and had at least one safety assessment. Cases.

In this study, baseline information was analyzed using FAS and PPS analysis. Primary efficacy indicators, secondary efficacy indicators, etc. were analyzed by both FAS and PPS. However, the conclusions obtained from FAS analysis were the main conclusions. When the conclusions from FAS and PPS are consistent, the credibility of the conclusions can be increased.

In the safety analysis, adverse events and adverse reactions, vital signs, and laboratory indicators were analyzed using SS. subjects who were terminated prematurely due to adverse events and various non-therapeutic reasons were included in the safety analysis.

**(2) Statistical analysis plan:** the analysis of the study results included the description of the distribution of subjects, the balance analysis of baseline indicators, the analysis of efficacy, and the analysis of safety.

Mean, standard deviation, median, quartile, minimum and maximum values were used for the statistical description of the measurement data. Comparisons between groups were performed by ANOVA or Kruskal-Wallis rank sum test, and comparisons in groups were performed by paired t-test or Wilcoxon signed rank test. test for within-group comparisons.

Statistical descriptions of counts and rank data used rate or composition ratio, comparisons of count data used  $\chi^2$  test or Fisher's exact probability method, and comparisons of rank data used Kruskal-Wallis rank-sum test.

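### The protocol gives three different references for rating adverse-event relatedness, and unblinded investigators do the rating, so adverse-reaction incidence is open to differential attribution between the cell and saline arms

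*Protocol*

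**What the plan says.** The protocol describes the causality rating in several places.

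- Section (16) item 8 (recording of adverse events) has all events recorded from consent to study end, whether or not the subject receives cells. It then asks the investigator to consider "combined medications and evaluate their relevance to DPSCs preparations".
- Section (16) item 3 (relevance): "The relationship between AEs and the study drug was judged according to five levels of" certainty, from definitely related to definitely unrelated, "and the incidence of adverse reactions was included in the first three levels". The reference here is the study drug.
- Section (15) item 1 (safety evaluation index): "Swollen and painful gums within one week after surgery, recorded as an adverse event, judged by the investigator to be an administration-related adverse reaction". The safety assessment in the scenario summary has the same rule with treatment-related as the label. Neither limits it to an arm.
- Section (XIX) item 2(1): "In the safety analysis, adverse events and adverse reactions, vital signs, and laboratory indicators were analyzed using SS". The safety set consists of cases that received the study drug. Item 2(2) gives chi-square or Fisher tests for count data.
- On blinding, the scenario summary says that "only periodontal data collection personnel and image data measurement personnel were kept blind", and section (V) item 3 agrees. Section (7) item 4 adds that "the researchers responsible for the safety and efficacy data analysis maintained blinding". That concerns analysis, not the rating of events.

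**The concern.** Whether an event counts as an adverse reaction depends on a judgement made by someone who knows the arm, against a reference that changes from section to section. A subject in the saline arm never receives the DPSCs preparation. Under section (16) item 8, an investigator who knows this has no basis for calling an event in that subject related. The same event after a cell injection can be called related.

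The protocol's own list of anticipated events in section (16) item 4 shows why this matters. Injection haematoma from local vessel damage is a needle injury and can occur in any arm. At the first injection, the volume, technique, anaesthesia and preceding scaling are the same in all arms, so the saline arm is the trial's measure of harm from the procedure itself. If its procedural events are not counted as reactions while those in the cell arms are, a comparison of adverse-reaction incidence can show a difference that comes from the rating rule and not from the product. Safety is part of the first study objective.

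**Working it through.** **1. The references side by side, applied to one event after a saline injection**

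| Place | Reference | Injection haematoma after saline | Gum swelling and pain within one week after saline |
|---|---|---|---|
| Section (16) item 8 | DPSCs preparations | cannot be related | cannot be related |
| Section (16) item 3 | study drug | related only if saline is a study drug | same |
| Section (15) item 1; scenario summary | administration / treatment | not covered | always an adverse reaction |

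The safety set in section (XIX) is defined by receipt of the study drug and must contain saline subjects if arms are to be compared. That supports the wide reading of item 3. Item 8 does not fit that reading.

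**2. How much it could matter**

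The protocol states no adverse-event rate and no attribution share, so there is no figure to reproduce. Everything below is an assumption apart from the planned arm sizes in section (8): about 33 saline, 33 single injection, 30 double injection, hence 33 + 30 = 63 on cells. Pooling the 63 is for illustration only.

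Let the true event incidence p be equal in all arms, and let shares a_T (cells) and a_C (saline) be rated related. Adverse-reaction incidences are then p × a_T and p × a_C. For example, p = 0.20 with a_T = 0.70 and a_C = 0 gives 0.14 against 0. The probability that a two-sided Fisher test gives p ≤ 0.05 follows by enumerating both binomials.

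| True incidence | 70% / 70% | 70% / 35% | 70% / 0% |
|---|---|---|---|
| 63 v 33: 10% | 3% | 3% | 7% |
| 63 v 33: 20% | 3% | 11% | 67% |
| 63 v 33: 30% | 4% | 21% | 97% |
| 63 v 33: 50% | 4% | 39% | nearly 100% |
| 33 v 33: 10% | 1% | 1% | 3% |
| 33 v 33: 20% | 2% | 6% | 31% |
| 33 v 33: 30% | 2% | 13% | 72% |
| 33 v 33: 50% | 3% | 26% | 99% |

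Columns give the shares rated related in the cell and saline arms. With equal shares the test stays at or below 4%. That also holds at 100% / 100%, which is what the gum-swelling rule does.

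**3. Extreme bound**

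Suppose every cell-arm event and no saline event is rated related.

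- Against 0/33, Fisher first reaches significance at 6/33 (p = 0.024; 5/33 gives 0.053) and at 4/30 (p = 0.046).
- P(X ≥ 6 | 33, p) = 11%, 67% and 96% at p = 10%, 20% and 30%.
- P(X ≥ 4 | 30, p) = 35%, 88% and 99% at the same rates.

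**The case against.** A reader might infer that saline subjects can hardly have an adverse reaction at all, and that the between-arm comparison is biased by construction. The documents do not support that, for four reasons.

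- The gum-swelling rule gives saline subjects adverse reactions automatically, and mild gum redness and swelling is the first local event that the protocol anticipates.
- The counting rule sits in section (16) item 3 and refers to the study drug, which can be read to include saline. Item 8 is about what to record, and its wording is visibly damaged in translation.
- All-cause adverse events are recorded and analysed in every arm, so the trial can still separate product from procedure.
- No between-arm test of adverse-reaction incidence is named. It follows only from the general methods for count data.

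Section (14) item 1, which also relates reactions to the stem cell preparations, is a suspension rule. Asking there whether the cells caused an event is reasonable, and it adds nothing to this point.

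The large percentages are also open to challenge. Section (III) reports no adverse reactions in 18 earlier subjects. The one-sided 95% upper limit is 1 − 0.05^(1/18) = 15%, or 1 − 0.05^(1/13) = 21% if only the 13 presumed cell recipients count (8 from the open study and 5 of the 10 randomized). Rates of 20% to 30%, gum swelling aside, therefore lack support in the protocol. These limits bound rated reactions, not all events, so they do not settle the event rate. Item 3 also steers events explained by non-drug factors towards unrelated, so full attribution in the cell arms is unlikely.

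These points narrow the concern but do not remove it. The conflict between items 3 and 8 remains, the raters know the arm, and the protocol gives all-cause incidence no priority over adverse reactions. Investigators make the rating as events are recorded, so a later analysis plan cannot repair it.

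**Conclusion.** The causality reference is inconsistent and must be reconciled. If section (16) item 8 governs, events in saline subjects other than gum swelling and pain within one week cannot be rated as related, while the same procedural event after cells can. Any between-arm reading of adverse-reaction incidence is then open to differential attribution. If the study drug in item 3 includes saline, that consequence does not follow, although raters would still know the arm.

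The size is not determined by the protocol. With 70% of cell-arm events rated related, the chance of a false difference is at most 7% at 10% incidence and grows with the event rate. At 50% incidence it reaches 39% if saline attribution is halved. The 67% to 99% figures in the extreme bound need full attribution in the cell arms, none in saline, and event rates of 20% to 30%, so they are an outer limit and not an expectation. All-cause incidence does not depend on the attribution, though reporting and grading in an open trial may still be affected by knowledge of the arm.

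**What to change.** - In section (16) items 3 and 8, use one arm-neutral reference: relatedness, in every arm, to the study injection (cells or saline) and its procedure.
- In section (XIX) item 2, make all-cause adverse-event incidence by arm the main between-group safety comparison. Report investigator-rated adverse reactions by arm descriptively.
- In section (15) item 1 and the scenario summary, keep gum swelling and pain within one week as a recorded event but list it separately from other reactions. Its fixed attribution also captures the effect of the scaling done on the same day.

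The cost is a change of wording in these sections and of one case report form label. No new data are needed, because all events are already collected in all arms. The small downside is that the headline harm rate will include unrelated events.
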